**Figure 1 F1:**
[figure not shown]
Research flow. The stages and flow of research are clearly described here.

### Intervention

The PTBLD PR programme will be held two times weekly for a period of 6 weeks. Each session will last approximately 2 hours, consisting of exercise and health education (online supplemental table 1). The PR programme recruitment will be rolling rather than fixed groups, with a maximum capacity of five patients per session (due to pandemic) and supervised by a nurse, doctor, researcher or physiotherapist. The equipment used will be simple and based on local availability. It will be based on the core elements of an evidence-based rehabilitation, including exercises and health education, but we will be adapting the detail and delivery based on the qualitative work in Stage 1.

10.1136/bmjopen-2021-048664.supp1Supplementary data

Core components of PR exercise are upper and lower body resistance training and aerobic training will be informed by international guidelines.^11 20^ The strength exercises will include (at least) bicep curls, pull-ups, sit-to-stands and step ups. Patients will be asked to do one session of strength training and to walk every day at home in addition to structured classes. Minimal equipment will be used where possible, such as bottles filled with water, to achieve the desired weight in kilograms and to offer insight into how participants can exercise effectively at home during and after finishing PR. Aerobic exercise will include walking and static cycling. Walking will be individually prescribed at a speed equivalent to 85% maximal oxygen capacity (VO_2_) peak derived from the ISWT.^21 22^ Walking will be monitored and target duration increased by the instructor as the programme progresses. The content delivered within the education sessions will be based on existing materials, with refinement from stage 1 of this trial and will be delivered by an interdisciplinary team.

### Usual care

As part of usual care, participants will receive their usual prescription medications (if appropriate), and an educational booklet regarding PTBLD and the importance of exercise, healthy diet, smoking cessation and avoiding biomass smoke.

### Sample size

#### Stage 1

We will conduct 8–10 focus groups of 2–10 patients (ideally 6–8 patients) in each group and up to 15 interviews with referrers to explore initial perceptions of PR and to inform the cultural adaptation of PR, for their insight, any minor modifications and any additional needs, so that it is suitable for this group and for understand their views on any specific topics for the health education component or any types of exercises that are suitable for enjoyment and adherence for this population.

#### Stage 2a

Assuming a statistical significance level of 5% and a statistical power of 80%, in order to detect a 35 m difference in ISWT measured at baseline and after completion of PR,^23^ a total of 114 participants are required (PR: 57 participants or waiting list control: 57 participants). This power calculation was performed using a paired t test and assumes the ISWT follows an approximately normal distribution. Data from a feasibility study in Uganda, assessing PR in a PTBLD population, have guided this calculation.^14^ Conservatively assuming up to 30% loss to follow-up at 6 weeks, this will require up to 114 participants to be recruited and randomised (1:1) to each arm. The estimated 70% ineligibility rate suggests approximately 543 patients with PTBLD will be screened for this trial.

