**Trial registration number:**

ISRCTN11122503.

Strengths and limitations of this studyThis project will inform an appropriate pulmonary rehabilitation programme for people living with post-tuberculosis lung disease (PTBLD) in Kyrgyzstan. This study is the first fully powered randomised controlled trial (RCT) of a culturally appropriate pulmonary rehabilitation programme for adults with PTBLD in Central Asia.This is a single-centre fully powered RCT; while findings will be important for assessing impact of pulmonary rehabilitation in Kyrgyzstan, Central Asia and low and middle-income countries (LMIC) more broadly, findings may not be generalisable to other parts of the world.Taking a mixed-method approach, this study will provide a rich insight into the experiences of pulmonary rehabilitation for people living with PTBLD.Using a common set of outcome measures specifically designed for pulmonary rehabilitation in LMIC will allow for direct comparisons of outcomes between sites across the world.

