### Data analysis

For stages 1 and 2b, qualitative data will be transcribed verbatim in Russian and translated into English for triangulation with UK-based researchers. Transcripts will be analysed using thematic analysis; following the six distinct stages of familiarisation with data; generating initial codes; searching for themes; reviewing themes; defining and naming themes and producing the report.^34 35^ The qualitative lead will carry out initial coding and a sample of the transcripts will be coded independently by a second researcher to improve consistency and interpretive authenticity. The team will meet regularly to review emerging themes, with close attention to interactions within the interview and focus group data.

For stage 2a, quantitative analysis will be conducted using Statistical Package for the Social Sciences. Data will be reported as mean (SD), median (IQR) or frequency (%) as appropriate. All randomised patients will be included in an intention to treat analysis with the primary efficacy analysis based on both per protocol and modified intention-to-treat populations, with missing data imputed. For the primary analysis, the differences in the primary outcome of walking distance on the ISWT will be estimated using mixed models (unadjusted and adjusted for covariates if there are differences between groups at baseline). There will be no formal interim analysis of the data.

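### The stated 80% power comes from a paired t test on before-after change and is not shown to apply to the between-arm comparison that the trial is run to make

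*Protocol article*

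**What the plan says.** All references are to the protocol article.

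- **Sample size, Stage 2a.** At 5% significance and 80% power, the target is a "35 m difference in ISWT measured at baseline and after completion of PR". The result is 114 participants, split as 57 for PR and 57 for the waiting list. The method is given as: "This power calculation was performed using a paired t test and assumes the ISWT follows an approximately normal distribution". The source is given as: "Data from a feasibility study in Uganda, assessing PR in a PTBLD population, have guided this calculation". No SD or correlation is printed.
- **Same paragraph, enrolment.** Allowing for up to 30% loss at 6 weeks, up to 114 are to be randomised to each arm. About 543 are to be screened, with 70% ineligible.
- **Trial design (Stage 2A) and Randomisation.** Participants are allocated 1:1 to PR or to usual care on a waiting list.
- **Data analysis.** For the primary analysis, "the differences in the primary outcome of walking distance on the ISWT will be estimated using mixed models", unadjusted and, if the groups differ at baseline, adjusted for covariates.
- **Abstract, Strengths and limitations, Background and rationale (including the objectives).** The trial is described as fully powered.

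**The concern.** The named test and the wording of the effect agree with each other: both describe change in the same people from baseline to after PR. Neither describes the comparison for which participants are randomised. The two arms contain different people, so there are no pairs across arms. For a given SD of change and a given number per arm, the difference between two mean changes has twice the variance of one mean change.

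The effect has the same problem. A 35 m gain in the PR arm is a 35 m benefit over usual care only if the control mean does not move. Controls receive a booklet that covers exercise, among other topics, and any change in their mean is subtracted from the PR gain.

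What is at stake is how a null result is read. A trial described as fully powered invites the reading that a non-significant result counts against PR. If power for the between-arm contrast is well below 80%, that reading is unsafe.

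**Working it through.** **Inputs.** From Sample size, Stage 2a: α = 5% (sidedness not stated; two-sided assumed), power 80%, difference δ = 35 m, 57 per arm, up to 114 randomised per arm, up to 30% loss, 543 screened, 70% ineligible. The SD and the baseline–follow-up correlation ρ are not given; values below are back-solved or assumed. Power uses the noncentral t distribution.

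**1. Can the stated 57 be reproduced?** Not directly, because no SD is given. It can only be inverted. For a paired t test the noncentrality is δ√n / SD. With n = 57, 80% power requires SD of change = 92.7 m (check: 35 × √57 / 92.7 = 2.85). The normal approximation gives 94.3 m.

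**2. Between-arm power at that SD.** The noncentrality is δ / (SD × √(2/n)).

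- n = 57 evaluable per arm: 35 / (92.7 × √(2/57)) = 2.02 on 112 df, so power is 51.5%.
- n = 80 evaluable per arm: 35 / (92.7 × √(2/80)) = 2.39 on 158 df, so power is 66%.
- For 80% power, 112 evaluable per arm are needed (111 by the normal approximation).

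**3. With baseline adjustment.** SD of change² = 2σ²(1 − ρ) and the adjusted residual variance is σ²(1 − ρ²). The working SD is therefore SD of change × √((1 + ρ)/2).

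| Assumed ρ | Working SD (m) | Power, 57 per arm | Power, 80 per arm |
|---|---|---|---|
| 0.5 | 80.3 | 64% | 78% |
| 0.7 | 85.5 | 58% | 73% |
| 0.9 | 90.3 | 54% | 68% |

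**4. If a two-sample test was in fact used.** Inverting the two-sample formula at 80% power gives SD = 66.1 m for 57 per arm and 78.5 m for 80 per arm. The difference detectable with 80% power at SD 92.7 m follows by proportion: 35 × 92.7 / 66.1 = 49 m with 57 per arm, and 35 × 92.7 / 78.5 = 41 m with 80 per arm.

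**5. Sensitivity to the unknown SD (unadjusted, δ = 35 m).**

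| SD (m) | Power, 57 per arm | Power, 80 per arm |
|---|---|---|
| 60 | 87% | 96% |
| 66 | 80% | 92% |
| 80 | 64% | 79% |
| 92.7 | 52% | 66% |
| 120 | 34% | 45% |

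**6. Which number per arm applies?** The paragraph supports two answers.

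- 114 randomised per arm, less 30%, leaves 114 × 0.70 = 79.8, about 80 evaluable per arm. Randomising 228 at 70% ineligibility would need 228 / 0.30 = 760 screened.
- The stated 543 screened matches 163 / 0.30 = 543, where 163 is 114 / 0.70, the required total inflated for loss. That returns to 57 evaluable per arm.

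Both columns therefore have to be shown until the enrolment number is reconciled.

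**The case against.** The best defence is that the word paired is a slip. The result is reported as 57 for PR and 57 for control, which is the form of a two-group calculation; a one-group paired calculation has no control arm. If a two-sample test on change was run with an SD near 66 m, the number is right and one word is wrong. This cannot be excluded. Nothing in the article confirms it, however, and the effect is also worded as a baseline-to-post difference. Even on this reading the published basis for the sample size needs correcting.

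Second, a journal article may leave the SD to the full protocol or to the cited feasibility study. That is accepted: the absence of the SD is not the fault here. It only means that the text cannot settle whether 80% holds.

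Third, 57 is the number required before loss, and the same paragraph allows up to 114 randomised per arm. With no loss at all, 114 per arm would give 81% even at 92.7 m. That stands as the favourable end, but the plan assumes up to 30% loss, and its screening figure fits the smaller enrolment.

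Fourth, the Data analysis section does not write that the mixed model compares arms. This is inferred from the randomised design, the effectiveness objective and the provision for baseline differences between groups. The inference is safe.

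**Conclusion.** The mismatch is established: the named test and effect describe within-person change, while the trial's primary question is a between-arm difference. The stated 80% is therefore not shown to apply to the primary comparison.

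The size of any shortfall is not established. On the literal paired reading with 57 pairs, power for a 35 m between-arm difference is about 52% to 66% unadjusted, for 57 to 80 evaluable per arm. Baseline-adjusted, it is 54–64% and 68–78% respectively, at assumed correlations of 0.9–0.5. If the relevant SD is about 66 m or less, there is no shortfall.

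A reader might infer that the trial is known to have about even odds of detecting its target. The documents do not support that: 92.7 m is back-solved, not stated, and 57 evaluable per arm is only one of two readings of enrolment. A reader might also treat all 114 as pairs, which implies an SD of 132.3 m and 29% power at 57 per arm. That fits poorly, because the article splits the 114 by arm and offers PR to controls only at the end of the study.

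**What to change.** Replace the paired calculation in Sample size, Stage 2a with a two-sample, baseline-adjusted calculation for the between-arm difference in 6-week ISWT.

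- State the target as a difference from usual care, with the sidedness of the test.
- Use the SD and the baseline–follow-up correlation from the feasibility study.
- Reconcile the enrolment number (114 per arm against about 163 in total) and base the calculation on it.
- Restate the power, or the detectable difference, that this number delivers.
- Qualify the description of the trial as fully powered, wherever it appears, if the result is below 80%.
- If a two-sample test was run all along, say so and give its SD.

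The cost is one recalculation and a rewritten paragraph. The correction itself requires no extra enrolment and leaves the planned mixed-model analysis as it is. The downside is that the stated power may turn out less favourable.

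### The recruitment target after 30% loss is wrong: the plan states 114 in total, then 114 per arm, while its 543 screened fits only about 163 randomised

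*Protocol article*

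**What the plan says.** All the relevant figures are in one paragraph of the Protocol article, Sample size, Stage 2a.

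- **Number required for power.** At a 5% significance level and 80% power, to detect 35 m on the ISWT, "a total of 114 participants are required (PR: 57 participants or waiting list control: 57 participants").
- **Allowance for loss.** "Conservatively assuming up to 30% loss to follow-up at 6 weeks", the text continues, "this will require up to 114 participants to be recruited and randomised (1:1) to each arm".
- **Screening.** "The estimated 70% ineligibility rate suggests approximately 543 patients with PTBLD will be screened for this trial".

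The Randomisation section confirms 1:1 allocation but gives no number. No other section gives a target adjusted for loss.

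**The concern.** The same number, 114, appears before and after the allowance for loss, first as a total and then as a figure for each arm. A 30% allowance can neither leave a sample size unchanged nor double it. The screening figure comes from a third number that is not printed.

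The number to randomise decides when the site stops recruiting. A reader of this paragraph could stop at 114, at about 163 or at 228, a two-fold range. The lowest leaves the trial short of its planned power under its own loss assumption. The highest randomises people whom the stated inputs do not call for. The article repeatedly describes the trial as fully powered, so the target behind that description should be unambiguous.

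**Working it through.** **Inputs, all from Sample size, Stage 2a:** 57 per arm (114 in total) required; power 80%; significance level 5% (sidedness not stated, two-sided assumed); loss 30%; ineligibility 70%; 543 screened; allocation 1:1.

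**Step 1. Can the plan's screening figure be reproduced?** Number randomised = evaluable / (1 − loss), and number screened = randomised / (1 − ineligible).

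- 114 / 0.7 = 162.9 randomised
- 162.9 / 0.3 = 542.9 screened, which matches the stated 543
- In reverse: 543 × 0.3 = 162.9 randomised, and 162.9 × 0.7 = 114.0 completers

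So 543 was most likely derived from 114 completers and about 163 randomised.

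**Step 2. Can the stated target be reproduced?**

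- Per arm: 57 / 0.7 = 81.4, rounded up to 82, so 164 in total.
- The common but incorrect inflation, n × (1 + loss), gives 57 × 1.3 = 74.1, so 75 per arm. From the total it gives 114 × 1.3 = 148.2, so 149.
- Neither method returns 114 per arm or 114 in total.
- Going from 57 to 114 per arm would need a loss of 1 − 57/114 = 50%.

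**Step 3. Which target fits 543 screened?**

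| Randomised in total | Screened (÷ 0.3) | Completers (× 0.7) |
|---|---|---|
| 114 | 380 | 79.8 (about 40 per arm) |
| 149 | 497 | 104.3 (about 52 per arm) |
| 163 | 543 | 114.1 (57 per arm) |
| 164 | 547 | 114.8 (57 per arm) |
| 228 | 760 | 159.6 (about 80 per arm) |

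Only 163, or 164 once the arms are made equal, agrees with 543 to within rounding.

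**Step 4. What happens to power?** No SD is given, but none is needed. The standardised effect is the one that yields 80% power at n = 57, and power is then recalculated at the reduced n. The paragraph names a paired t test while the trial compares two arms, so both forms were run with the t distribution.

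| Reading of n = 57 | Effect giving 80% | Power at 40 | Power at 80 |
|---|---|---|---|
| Two-sample, per arm | 0.529 | 0.647 | 0.914 |
| Paired | 0.378 | 0.644 | 0.916 |

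A normal approximation agrees. The noncentrality at 80% power is 1.96 + 0.84 = 2.80. At 40 per arm it becomes 2.80 × √(40/57) = 2.35, and Φ(2.35 − 1.96) is about 0.65.

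**Step 5. How large is the excess at 228?** 228 − 164 = 64 people.

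**The case against.** The strongest counter-argument is that 114 already includes the loss. Since 40 / 0.7 = 57.1, the calculation might have required 40 evaluable per arm, and 57 per arm would be the inflated number. Without a stated SD this cannot be excluded: 57 evaluable per arm implies an SD of about 66 m in a two-sample calculation, and 40 per arm implies about 55 m. On that reading, stopping at 114 in total would keep 80% power.

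Two things count against it. The text gives 114 as the number required for 80% power before it mentions loss. And the reading does not rescue the paragraph: the words assigning 114 to each arm would still be wrong, and 543 would deduct the 30% twice, where 114 / 0.3 = 380 would be right.

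It is also fair to say that the power loss is conditional. Followed literally, 114 per arm gives an oversized trial rather than an underpowered one. The full protocol, which is not shown, may carry the correct target. That does not excuse the article, which has not left a figure out but has printed figures that contradict each other.

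What stands of this objection is that 82 per arm is the most likely reconstruction, and the sponsor should confirm it before adopting it.

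**Conclusion.** The point holds. The three figures cannot all be true, and the sentence giving the target after loss is wrong whether 114 is taken as a total or per arm. On the text as written, the target consistent with both the power requirement and the screening figure is 163 to 164 randomised.

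The fall in power to about 64–65% rests on three conditions: 57 per arm is the evaluable number, recruitment stops at 114 in total, and the full 30% is lost. The arithmetic on loss and screening needs none of these beyond the plan's own percentages. Whether 57 is itself the right base, given the missing SD and the paired test, is a separate question and is not settled here. The correction is needed because the paragraph does not fix a recruitment target.

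**What to change.** Check the source calculation to confirm that 57 per arm is the number before loss, then replace the paragraph's figures with one chain. Suggested wording:

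*Fifty-seven evaluable participants per arm (114 in total) are required. Allowing for 30% loss to follow-up at 6 weeks, 82 per arm (164 in total) will be randomised 1:1. With an estimated 70% of those screened ineligible, about 547 people will be screened.*

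State the SD beside the 35 m difference so that the 57 can be reproduced. If the base number changes, carry it through the same two divisions (by 0.7, then by 0.3). Use the same target wherever it appears in the trial documents.

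The cost is rewording. The screening figure rises by only 4, from 543 to 547, because the stated 543 already corresponds to about 163 randomised.

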#### Stage 2b

We will conduct up to five focus groups of 2–10 patients (ideally 6–8 patients) and an interview with all members of the PR delivery team. All participants randomised to the PR group will be asked to complete the log book and evaluation form.

### Randomisation

Randomisation will occur through a web-based service Sealed Envelope and conducted in a designated room by a dedicated member of the research team. Participants will be randomised (1:1) to either PR or usual care. A dedicated member of the research team will inform the assessors of group allocations via telephone. Participants will be informed at the end of their baseline visit to arrange their first PR class.

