Explore the views of people living with PTBLD and HCPs (referrers and deliverers) involved in the care of patients living with PTBLD to inform the adaptations needed for a PR programme suitable for people living with PTBLD in Kyrgyzstan.Conduct a single-blind fully powered RCT to assess the effectiveness of adapted 6-week PR on maximal exercise capacity (assessed by the incremental shuttle walking test (ISWT)).Evaluate a range of secondary outcome measures including health-related quality of life, respiratory symptoms, functional status and psychological well-being following PR.Assess any further changes in all outcome measurements 12 weeks postbaseline.Assess the acceptability of PR of participants and the staff delivering PR to inform further improvements to the service.

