### Procedure

After receiving a research fact sheet, patients eligible for the study will be asked if they would like to participate after they have had the opportunity to ask questions. If they wish to take part, they will be asked to provide written informed consent (Appendix A). Reasons for declining the study will be taken as field notes. If they wish to participate, they will be asked to provide written informed consent. Reasons for declining to participate will be reflected in the field notes. The staff of the family medicine centres, doctors of the City Tuberculosis Hospital, the City Tuberculosis Dispensary, the National Hospital, District Hospitals and the National Centre of Cardiology and Internal Medicine will screen patients for eligibility and refer interested patients to the PR study team. Interested patients will be screened by the study team to confirm interest in participation and to schedule the baseline visit. After providing written informed consent, participants will undergo a baseline assessment at the NCCIM by a specially trained team of researchers and residents. After the baseline measures are complete, participants will be randomised into one of two groups: PR or usual care control. At 6-week postbaseline and 12-week postbaseline, patients will undergo follow-up assessments. If participants are not able to attend follow-up assessments in person, questionnaires only will be completed via telephone appointment. Experiences of the patients living with PTBLD and PR deliverers will be explored in interviews and focus groups. Participants who drop out of the trial will be asked to take part in an interview and information provided freely by the participants will be collected as field notes. All outcome measures will be performed at 6 and 12 weeks by dedicated staff who are blinded to group allocations. Control participants will be offered PR at the end of the study (see figure 1).

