### Blinding

Outcome measures taken at baseline, post-PR and follow-up will be taken by a researcher blinded to group allocation. It is not possible to blind participants to treatment due to the nature of a PR intervention. Research staff will be blinded to outcome measures. Participants will be advised not to reveal their group during the follow-up assessments. Episodes of un-blinding will be documented and reported for both time points.

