#### Primary outcome

The primary outcome of exercise capacity will be measured using the ISWT.^21^ The ISWT will require patients to walk up and down a 10-metre course marked out using cones at walking speeds dictated by an audio signal played on an audio device. Each participant will receive standardised instructions to: ‘Walk at a steady pace, aiming to turn around when you hear the signal. You should continue to walk until you feel that you are unable to maintain the required speed without becoming unduly breathless’. To account for any learning effect, a practice ISWT will be performed and the greatest distance walked from either test will be taken forward. The test will be terminated when either: (1) the patient indicates that they are unable to continue, (2) the operator determines that the patient is not fit to continue or (3) the operator assesses that the patient was unable to sustain the speed and cover the distance to the cone prior to the beep sounding.

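### The Randomisation section has allocations telephoned to the assessors, which as worded conflicts with the assessor blinding stated elsewhere and leaves unclear who may learn the allocation

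*Protocol article*

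**What the plan says.** Four sections of the protocol article bear on who knows the allocation.

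- **Design.** The objectives, listed under Background and rationale, describe the trial as single-blind: "Conduct a single-blind fully powered RCT to assess the effectiveness of adapted 6-week PR on maximal exercise capacity".
- **Procedure.** Baseline assessment is carried out by a trained team of researchers and residents, and randomisation follows once it is complete. For the later visits: "All outcome measures will be performed at 6 and 12 weeks by dedicated staff who are blinded to group allocations".
- **Randomisation.** "A dedicated member of the research team will inform the assessors of group allocations via telephone". The next sentence deals with telling participants at the end of the baseline visit.
- **Blinding.** "Outcome measures taken at baseline, post-PR and follow-up will be taken by a researcher blinded to group allocation". On participants: "It is not possible to blind participants to treatment due to the nature of a PR intervention". As a safeguard: "Participants will be advised not to reveal their group during the follow-up assessments". Un-blinding episodes are to be recorded for both time points. The section also contains this sentence: "Research staff will be blinded to outcome measures".

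The Primary outcome section gives three ways for the ISWT to end. One is the patient's own decision ("the patient indicates that they are unable to continue"). The other two are decisions by the operator: that the patient should not go on for reasons of fitness, or that the patient has lost the pace.

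**The concern.** A person who has been telephoned the allocation is not blinded to it. The Randomisation section names the recipients of the call simply as the assessors. The other two sections promise that assessors do not know the allocation.

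The stake is the trial's whole claim to blinding. Participants know their group, so the word single-blind can refer only to the people who measure outcomes. Those people run a walking test in which two of the three stopping conditions rest on their own judgement and the third on patient effort. An operator who knows the group could, without intending to, be quicker or slower to stop the test. Bias that enters at measurement cannot be removed in the analysis.

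The sentence that research staff are blinded to outcome measures does not help. It concerns knowledge of outcomes, not of allocation, and the article does not define which staff it covers.

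**Working it through.** No arithmetic decides this point. It is a comparison of the sections, in four steps.

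**1. Who is blinded?** The Blinding section rules out participants. The Procedure and Blinding sections name the outcome assessors. No other party is said to be blinded to allocation, so assessor blinding is the only blinding the trial has.

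**2. Who is told?**

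| Section | Who | Knows the allocation? |
|---|---|---|
| Randomisation | The assessors, with no visit specified | Yes, by telephone |
| Procedure | Dedicated staff at 6 and 12 weeks | No |
| Blinding | The researcher taking outcomes at baseline, post-PR and follow-up | No |

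Read literally, the first row contradicts the other two.

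**3. Can the rows be reconciled?** They can if the assessors who take the call are the baseline staff only and other people do all the follow-up testing. The baseline measures come before randomisation, so they are taken without knowledge of the allocation whoever is told afterwards. The follow-up measures then stay blinded if the follow-up staff are different people. This reading needs two facts:

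- the call goes to baseline staff only;
- those staff do not test the same participants at 6 or 12 weeks.

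The article states neither. The Procedure section describes the baseline and follow-up teams in different words but does not say that they are different people. The Blinding section refers to a blinded researcher across all three time points.

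**4. Does the literal reading fit the rest of the plan?** It does not. Advising participants to keep their group to themselves, and logging un-blinding episodes, would have little purpose if the assessors had already been told. This suggests that the Randomisation sentence is loosely drafted and that un-blinding is not intended. It is still the only sentence that says where the allocation goes, so it is the one that site staff would follow.

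**The case against.** The strongest objection is that the sections can coexist. Randomisation comes after baseline, and the sentence after the telephone call concerns the end of the baseline visit. The natural recipient of the call is therefore whoever is with the participant on that day. The Procedure section reserves the 6- and 12-week measures for dedicated blinded staff. The intended blinding is stated twice, and a fuller protocol may name the roles.

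Much of this stands. A reader might infer that the Randomisation and Blinding sections cannot both be followed, or that the trial plans to un-blind its outcome assessors. The article does not support either inference, since a compatible reading exists. What the objection does not supply is any statement that the baseline and follow-up assessors are separate people. Nor can the conflict be put down to an article's brevity, because the problem is a sentence that is present, not a detail that is absent.

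Three further inferences should also be resisted.

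- **A size for the bias.** The course is 10 m long and the Sample size section targets 35 m, so one shuttle is 10/35 = 29% of the target and two are 20/35 = 57%. These figures set an error in one patient against a difference in means. To shift the mean contrast by 10 m, assessors would have to move it by a full shuttle per patient on average, always in the same direction. Nothing in the article indicates that. Operator discretion is also limited, because one stopping condition is the patient's own and another is tied to reaching the cone in time.
- **Overlap between PR supervisors and assessors.** The Intervention section lists a researcher among those who may supervise sessions, and the Blinding section has a researcher taking outcomes. No section says that these are the same people.
- **A definite error in the sentence on research staff and outcome measures.** It may mean that staff who randomise or deliver PR do not see follow-up results. Walking is prescribed from the ISWT, so whoever prescribes it needs the baseline result and the sentence cannot apply to everyone. It is loose, but its meaning is uncertain and it has not been shown to be wrong.

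**Conclusion.** The point holds as an inconsistency in the text that needs correcting. The Randomisation section, as worded, sends the allocation to the assessors, while the Procedure and Blinding sections say that outcome assessors do not have it. A benign reading is available and may well be the intended one. It depends on a separation of staff that the article does not state.

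The consequence is a risk, not a demonstrated bias. If the sentence were followed literally, the trial would lose its only blinding, and a primary outcome that operators can end on judgement would be open to assessor bias. The size of that bias cannot be estimated: the article gives no standard deviation for the ISWT and nothing on how far knowledge of the allocation might move the measurement.

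The conclusion rests on the wording of the article alone. It would be answered if the full protocol names who takes the call and keeps that person away from the later assessments.

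**What to change.** - **Randomisation section.** State that the allocation is given only to the participant and to the staff who book or deliver PR, and not to outcome assessors. If a baseline assessor must pass on the allocation at the end of the visit, state that this person does not assess that participant at 6 or 12 weeks.
- **Blinding section.** Make it consistent with this: baseline measures are taken before randomisation, and the 6- and 12-week measures are taken by staff who have not been told the allocation. Clarify the sentence on research staff by saying which staff are meant and which outcome results they do not see.

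The cost is a few sentences and possibly a change in who answers the telephone. The Procedure section already plans dedicated blinded staff for follow-up, so the design, sample size and analysis do not change. A single-centre team may need a simple record of who took each call, so that follow-up visits can be assigned to someone else. The change is worth making before follow-up assessments begin, because lost blinding cannot be restored afterwards.
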